### Effectiveness outcomes

#### Primary outcome

*Healthcare system burden*, measured as the number and length of hospital admissions from the initial visit to death or study exit. Data on health care utilisation will be prospectively recorded by registering events since the last visit at each study visit and compared to a recent historic cohort of a similar size from the involved centers.

Hospital admissions will be categorised into three mutually exclusive groups:

*Liver-related admissions*: inpatient stays of ≥ 24 h due to complications of liver cirrhosis, including variceal bleeding and other bleeding related to portal hypertension, hepatic encephalopathy, spontaneous bacterial peritonitis, hepatorenal syndrome, alcoholic hepatitis, ascites, infection, electrolyte imbalances, increasing frailty, sarcopenia, or poor nutritional status.*Non-liver-related admissions*: inpatient stays of ≥ 24 h for conditions not directly related to cirrhosis.*Short admissions*: hospital stays of < 24 h, excluding admissions in which paracentesis is the sole intervention.

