**Methods:**

The LiverCare study is a multi-center, mixed-method, pragmatic, non-randomised clinical study with a hybrid type 1 effectiveness-implementation design. The study is conducted in hepatology departments across four hospitals in three of Denmark’s five regions. It is guided by the British Medical Research Council and Reach, Effectiveness, Adaption, Implementation, Monitor frameworks and includes both a feasibility study and a mixed-method process evaluation.

The LiverCare intervention is grounded in a palliative approach, emphasising open, exploratory palliative care conversations. The intervention is integrated into routine outpatient care and the palliative care conversations are delivered by hepatologists and liver nurses who attended a specially designed course within palliative care. Eligible participants are adults with decompensated liver cirrhosis of any etiology who meet at least one general and one disease-specific palliative care indicator, assessed using the Supportive and Palliative Care Indicators Tool. Informal caregivers are invited to participate in the intervention.

Palliative care conversations are initiated following a formal invitation and continue after four to ten weeks and then every six months up to 36 months or until study withdrawal or death. The primary outcome is healthcare utilization, defined as the number and length of hospital admissions, compared to a historic cohort. Secondary outcomes include outpatient contacts, symptom burden, quality of life, and caregiver burden. The study also includes cost-effectiveness and cost-utility analysis.

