#### Exclusion criteria include

Inability to provide informed consent or comply with the study protocol.Diagnosis of advanced malignant disease other than hepatocellular carcinoma.Current contact with specialised palliative care services or hospice.Being listed for liver transplantation.

Eligible patients are invited to participate by a hepatologist or specialised liver nurse, either during hospitalisation or at an outpatient visit. Participation is voluntary, and patients are informed that they may withdraw consent at any time. Patients are encouraged to nominate an informal caregiver to participate in the study. Informal caregivers can include family, close friends, or any other person chosen by the patient. To be eligible, the informal caregiver must be at least 18 years old, be able to speak and understand Danish, and available to participate in at least one study visit. After receiving oral and written information, patients are given at least 24 h to consider participation. If the patient agrees, the first study appointment is scheduled.

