#### Documentation and actions

The Palliative Care Conversations conclude with a summary of the main points, including agreed-upon care goals and priorities. These are documented in the medical record to inform ongoing care.Based on the conversation, the healthcare professional may initiate relevant actions, including but not limited to:Pharmacological treatment adjustments or medication titration.Referral to psychosocial support services (e.g., chaplain, psychologist).Referral to primary care, rehabilitation services, specialized palliative care teams, or hospices.Coordination or communication with informal caregivers, primary care providers, or public services.

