**Health economic outcomes**

*Cost-effectiveness analysis*, based on the number and length of hospital admissions per patient during the follow-up period.*Cost-utility analysis*, assessing the cost per Quality-Adjusted Life Year (QALY) based on the results of EQ-5D-5 L data.

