### Implementation outcomes

An overview of the process indicators and methods of measurement for the feasibility study and process evaluation are presented in Table 1.

**Table 1 Tab1:** Overview of process indicators and methods of measurement and data collection

Domain	Method	Process indicators	Data sources
Reach and uptake	Descriptive quantitative evaluation	Number of patients referred for the intervention Number of patients included of all eligible Referral patterns	Screening data
Effectiveness	Preliminary quantitative evaluation of endpoints in Phase 2 and quantitative evaluation of endpoints in Phase 3 Cost-effectiveness analysis Cost-utility analysis	Number and length of hospital admissions Patient reported outcomes Change in caregiver burden Staff time, training, materials Healthcare utilization QALYs gained	Medical records PRO-Pall EQ-5D-5 L ZBI Danish DRG tariffs EQ-5D-5 L
Adoption		Proportion of sites offering the intervention	Information from study sites
		Differences in implementation between implementation sites	
*Implementation:* Feasibility: *The degree to which the intervention can be carried out in a given setting.*	Mixed-method evaluation Descriptive quantitative evaluation Qualitative evaluation	Resource utilisation Palliative care planning processes No. of invitation leaflets handed out to participants and families No. of palliative conversations per participant No. of informal caregivers participating in palliative conversations. No. of PRO-Pall questionnaires completed for each palliative conversation. No. of medical interventions. No. of patients referred to palliative care teams No. of patients referred to hospices No. of patients referred to municipal offers (exercise, nutrition, alcohol treatment, etc.) Patient experience Caregiver experience Healthcare personnel experience	Self-developed questionnaire with open-ended questions on experiences with palliative care, pre-study training, and the intervention
*Fidelity: The degree to which the intervention was implemented as intended.*			Informal conversations with health care professionals
Acceptability and Appropriateness: *The perception among implementation stakeholders that a given intervention is agreeable*,* palatable*,* or satisfactory.*			Semi-structured interviews informal caregivers and patients
			Medical records
			Semi-structured qualitative interviews

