### Statistical methods

All data will be entered into a shared REDCap database [42]. Descriptive statistics for numerical data will be presented as means with standard deviations (SD) for normally distributed variables, or as medians with interquartile ranges (IQR) for non-normally distributed variables. Categorical data will be presented as counts and proportions. For between-group comparisons, unpaired two-sample Student’s *t*-tests will be used for normally distributed numerical data, and the Wilcoxon-Mann-Whitney test for non-normally distributed numerical data. Categorical variables will be compared using the chi-squared test. Differences between groups will be reported as means with standard errors (SE) and 95% confidence intervals (CI) for numerical outcomes, and as odds ratios (OR) with 95% CI for dichotomous outcomes. All statistical analyses will be conducted using Stata Statistical Software, version 16 (StataCorp, College Station, Texas). Missing data will be reported and explored. Where appropriate, multiple imputation techniques will be considered. Both intention-to-treat (ITT) and per-protocol analyses will be conducted to assess robustness of findings.

The cost-effectiveness analysis will include cost and effect. The costs will include intervention-related expenses (e.g. staff time, training, materials) while the effect will include the use of healthcare resources using Danish DRG standard tariffs.

The cost-utility analysis will be based on the EQ-5D-5 L-data and the values will be converted to utility scores using Danish population-based value [43]. These scores will be used to estimate QALYs, which will serve as the measure of effectiveness.

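### The primary outcome is named as system burden but counts hospital stays only, so care moved to hospice could not be told apart from a real reduction

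*Protocol article*

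**What the plan says.** Under Primary outcome, the protocol article defines *Healthcare system burden* as "measured as the number and length of hospital admissions from the initial visit to death or study exit". It splits admissions into liver-related, non-liver-related and short, all of them hospital stays. The comparison is with the past: "compared to a recent historic cohort of a similar size from the involved centers". The abstract gives the same content under a different name: "The primary outcome is healthcare utilization, defined as the number and length of hospital admissions, compared to a historic cohort".

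Under Documentation and actions, the steps that a professional may take after a conversation include "Referral to primary care, rehabilitation services, specialized palliative care teams, or hospices". The exclusion criteria remove patients with "Current contact with specialised palliative care services or hospice", so hospice use in the intervention group starts after entry.

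Hospice appears as a measure in one place, among the implementation indicators of Table 1: "No. of patients referred to hospices". The secondary outcomes add outpatient visits, ascites contacts and telephone calls, but no hospice stays.

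Under Health economic outcomes, the cost-effectiveness analysis is "based on the number and length of hospital admissions per patient during the follow-up period". Statistical methods words it more broadly: "the effect will include the use of healthcare resources using Danish DRG standard tariffs".

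**The concern.** The name of the outcome promises more than it counts. The intervention has a route that can take a patient out of the setting where the outcome is measured. A patient who spends two weeks in hospice instead of on a hospital ward lowers the primary outcome by two weeks, although inpatient care has only changed place. With no hospice days in either cohort, the analysis cannot show how much of a fall is relocation.

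Two conclusions are exposed: a claim that the burden on the health system fell, and a favourable cost-effectiveness result built on the same hospital admissions. A result stated as fewer days in hospital is not exposed.

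**Working it through.** **1. The plan's own figure.** Sample size assumes 7 hospital days per year in the historic cohort, a reduction of 2 and an SD of 7, and states 199 participants. Alpha and power are not given; I assume two-sided 5% and 80%.

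- n per group = 2 × (1.960 + 0.842)² × 7² / 2² = 192.3, so 193 (194 with the t distribution).
- At 199 per group the standard error is 7 × √(2/199) = 0.70 days and power is 81%.

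The stated 199 is therefore reproduced approximately, as a per-group figure. The present point does not change it.

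**2. Mean follow-up (assumption).** The Introduction gives a median survival of about two years after decompensation, and follow-up runs to 36 months. With exponential survival the rate is ln 2 / 2 = 0.3466 per year. Mean follow-up = (1 − exp(−0.3466 × 3)) / 0.3466 = 1.865 years.

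**3. Days displaced (assumption).** The article gives no hospice rate, stay or displacement ratio. Suppose each hospice day replaces one hospital day, and only hospice use in excess of the historic cohort counts. Then

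fall in hospital days per patient-year = excess share of patients × hospice stay / 1.865.

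| Excess share over follow-up | Stay (days) | Fall (days/year) | Share of the 2-day effect |
|---|---|---|---|
| 5% | 10 | 0.27 | 13% |
| 10% | 14 | 0.75 | 38% |
| 10% | 20 | 1.07 | 54% |
| 20% | 14 | 1.50 | 75% |
| 20% | 20 | 2.14 | 107% |

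For scale, 7 days per year over 1.865 years is about 13 hospital days per control patient. The top row of assumptions (20% × 20 = 4 days) would remove about 31% of them. If the excess share is read as a share per year, the division by 1.865 drops out and 10% × 20 days becomes 2.0 days per year instead of 1.07.

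**4. Consequence for the test.** Suppose total inpatient days (hospital plus hospice) do not change at all. At 199 per group with SD 7, the chance of a significant fall in hospital days is Φ(shift / 0.70 − 1.96):

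- 0.5 days displaced: 11%
- 1.0 day: 30%
- 1.5 days: 57%
- 2.0 days: 81%

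**5. Would any other listed measure separate the two?** The referral count shows whether patients were referred, but not whether they were admitted or for how long, and no counterpart is described for the historic cohort. The secondary outcomes do not include hospice stays. The cost-effectiveness measure uses the same hospital admissions as the primary outcome.

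**The case against.** The strongest defence is that the outcome is defined openly wherever it appears. The aim speaks of hospital admissions and the sample size of days in hospital, so nothing is miscalculated. Moving care out of hospital can be a legitimate goal of palliative care, and hospital days are a sound outcome under that name. All of this stands. It does not support the broader name, or a claim about the system as a whole.

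Several stronger readings are tempting, and the article does not support them.

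- *Hospice use is left out of the economic analysis.* A reader might infer this from the DRG tariffs and the admission-based definition. But Statistical methods speaks of use of healthcare resources, and Table 1 lists healthcare utilization apart from admissions. Inclusion is unclear, and item-level costing may sit in a fuller document.
- *A hospice patient stays in follow-up and accrues zero days.* The article does not say whether hospice entry counts as study exit. Either way, the hospice days are not counted.
- *The intervention sends patients to hospice.* Referral is optional and one action among several.
- *The effect falls mainly in the terminal phase.* The article does not say so; its care model spans four trajectories, beginning with the chronic one.
- *Substitution would explain a third to all of the effect.* That depends on starting the range at 10% of patients. Lower inputs give far less, and a hospice day may replace a day at home.

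It is also fair that resting the burden claim on total inpatient days alone would in effect replace the measure the trial was sized for. If hospital days fall by 2 and 0.5, 1.0 or 1.5 of these are displaced, the net fall is 1.5, 1.0 or 0.5, and power at 199 per group (SD still 7) drops to 57%, 30% or 11%.

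**Conclusion.** The point holds as a mismatch between the name of the primary outcome and what it counts, together with a possible route by which the intervention shifts care out of the count. As described, the primary outcome and the admission-based cost-effectiveness measure cannot separate fewer inpatient days from relocated ones.

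The size is unknown. Under the stated assumptions (exponential survival with a two-year median, one-for-one displacement, an excess over the historic cohort of 5% × 10 days to 20% × 20 days) it is about 0.3 to 2.1 days per year against the hypothesised 2. That range shows the issue could matter; it is not evidence that it does. Results stated as hospital use remain valid in this respect. This is a worthwhile, inexpensive improvement and not a fault in the sample size.

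**What to change.** - Keep hospital days as the primary outcome and as the basis of the sample size. Name it hospital use in the abstract and in the outcome section, and limit the primary conclusion to that.
- Record hospice inpatient days (admission and discharge dates) in both cohorts where available.
- Prespecify hospital plus hospice days as a supporting analysis, required before any claim of reduced system burden. Report it as an estimate with a confidence interval, since the trial is not sized for it.
- State whether hospice entry ends outcome follow-up, and apply the same rule to both cohorts.
- Include hospice days in the economic costs for both cohorts.

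The cost is extra data extraction and some rewording. Hospice dates may be incomplete for the historic cohort, because the article does not show that hospital records hold them. The extent of missing dates should be reported; if it is large, the conclusion stays with hospital use alone.

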### Intervention elements

The intervention is delivered alongside standard care and integrated into patients’ regular clinical appointments. In all participating settings, standard care involves routine follow-up of patients with cirrhosis by a team of hepatologists and specialised liver nurses. Following an admission due to decompensated cirrhosis, patients are routinely offered planned follow-up in an outpatient clinic.

The initial palliative care conversation is conducted by a hepatologist in collaboration with a specialised liver nurse. Alternatively, the conversation may be conducted solely by the liver nurse. Subsequent conversations are conducted by either a hepatologist or a liver nurse after 4–10 weeks, and at 6, 12, 18, 24, 30, and 36 months, or until withdrawal from the study or death. Extra visits may be scheduled if clinically indicated or if the patient or informal caregivers request additional support or planning.

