## Sample size and statistical methods

### Sample size

The study aims to include 240 patients and 100 informal caregivers, based on sample size calculations for the most significant outcomes and to accommodate expected attrition.

The Healthcare System Burden will be measured as the number and length of admissions. Patients with cirrhosis spend an average of seven days per year in hospital [39]. Health care utilization data from the intervention group will be compared to a recent historical cirrhosis cohort. For the sample size calculation, we assumed the historical cohort will have an average of seven days in hospital per year and hypothesize that the intervention will cause a reduction of two days/year with an assumed SD of 7 days. Hence, 199 participants are required (STATA BE 18.5). With an estimated attrition rate of 20%, we aim to include 240 patients [40, 41].

Caregiver burden will be measured using the 22-item ZBI (range 0–88). A change of 5 points is considered realistic and clinically relevant. Based on previous studies, this change can be detected with 100 informal caregivers if the standard deviation (SD) of the change is around 14 [35, 36].

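### The primary outcome stops at study exit and is recorded at study visits, so admissions after withdrawal fall outside it in the intervention cohort, a cut-off a historic cohort cannot share

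*Protocol article*

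**What the plan says.** The Primary outcome section counts admissions and their duration "measured as the number and length of hospital admissions from the initial visit to death or study exit". On capture it says: "Data on health care utilisation will be prospectively recorded by registering events since the last visit at each study visit". The comparison is with historic patients: "compared to a recent historic cohort of a similar size from the involved centers".

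The visits that carry this recording have a stated end. The abstract has the conversations continuing "every six months up to 36 months or until study withdrawal or death", and Intervention elements repeats the rule: "or until withdrawal from the study or death". The eligibility section adds that "patients are informed that they may withdraw consent at any time".

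Loss of patients is expected. The Sample size section states: "With an estimated attrition rate of 20%, we aim to include 240 patients". Statistical methods then promises: "Both intention-to-treat (ITT) and per-protocol analyses will be conducted to assess robustness of findings".

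The article does not define study exit. It describes no follow-up after exit, and it gives no start or end of follow-up for the historic cohort. Table 1 lists medical records among the data sources for effectiveness, without saying whether they are read beyond exit.

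**The concern.** Both the definition of the outcome and the way it is captured end when a patient withdraws. An ITT analysis in a study without randomisation can only mean all enrolled patients over the intended follow-up. For a patient who withdraws, part of that follow-up is outside the outcome by definition. Multiple imputation, which the plan only considers, does not clearly help: under this definition later admissions are excluded from the outcome, not missing from it.

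Nobody can withdraw from a historic cohort, so the rule shortens one side of the primary comparison only. There are two consequences:

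- A count of admissions or a total of days is lower in the intervention cohort simply because less time is observed.
- If patients tend to leave when hospital use is high, or about to be, even a rate per person-time is lowered. In decompensated cirrhosis, with a median survival of about two years according to the Introduction, this is plausible.

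Either would look like benefit. The same admissions data feed the cost-effectiveness analysis.

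**Working it through.** **Inputs from the article (Sample size section).** Historic mean 7 days/year, target reduction 2 days/year, SD 7, 199 required, attrition 20%, target 240.

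**The plan's own figures.** Alpha, power and allocation are not stated. Assuming a two-sided 5% level, 80% power and two equal groups, a t-based two-sample calculation needs 194 per group. The stated 199 is within 3% of that and gives 81.3% power. The 240 matches 199 × 1.2 = 239. These figures do not decide this point, but they show the planned loss: 240 × 0.20 = 48 patients, leaving 192.

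**Bias in a rate.** Assume no true effect. Let f be the share of intended person-time lost after withdrawal, and k the rate in the lost time divided by the overall average. Then:

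- observed rate = 7 × (1 − f × k) / (1 − f)
- spurious reduction = 7 − observed rate

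Neither f nor k is in the article. Two values of f are assumed, with all 20% attrition taken as withdrawal:

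- 20% leave with half of their follow-up remaining: f = 0.20 × 0.50 = 10%
- 20% leave with 15% of it remaining: f = 0.20 × 0.15 = 3%

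| f | k | Observed days/year | Spurious reduction | Share of 2-day target |
|---|---|---|---|---|
| any | 1 | 7.00 | 0 | 0% |
| 3% | 2 | (7 − 0.42)/0.97 = 6.78 | 0.22 | 11% |
| 3% | 3 | (7 − 0.63)/0.97 = 6.57 | 0.43 | 22% |
| 10% | 1.5 | (7 − 1.05)/0.90 = 6.61 | 0.39 | 19% |
| 10% | 2 | (7 − 1.40)/0.90 = 6.22 | 0.78 | 39% |
| 10% | 3 | (7 − 2.10)/0.90 = 5.44 | 1.56 | 78% |
| 10% | 0.5 | (7 − 0.35)/0.90 = 7.39 | −0.39 | −19% |

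The last row shows that the sign reverses if the patients who leave are the healthier ones.

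**Bias in a total.** The share of days lost is f × k. With f = 10% and k = 1, a total is 10% too low although withdrawal is unrelated to admissions. With k = 2 it is 20% too low.

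**Cross-check by simulation, no true effect.** The inputs are again assumed: gamma-distributed rates with mean and SD 7 days/year, a death hazard of about 0.35/year that rises with the rate, a 36-month horizon, and 20% withdrawing in the intervention cohort only.

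| Withdrawal | Total days per patient, full → cut | Fall in total | Days per person-year, full → cut |
|---|---|---|---|
| Unrelated to rate | 11.61 → 10.17 | 12% | 5.77 → 5.84 |
| Moderately related | 11.66 → 9.57 | 18% | 5.79 → 5.46 |
| Proportional to rate | 11.65 → 9.00 | 23% | 5.80 → 5.12 |

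The spurious reduction in the rate is thus about 0 to 0.7 days/year, which agrees with the low to middle part of the first table.

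**The case against.** The strongest reply is that the article says less than a critic might read into it. Four inferences are tempting, and the text supports none of them.

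- *Stopping the conversations means leaving the study.* Intervention elements says that withdrawal ends the conversations, not the reverse. A planned per-protocol analysis, and a count in Table 1 of conversations held with each participant, suggest that patients with incomplete exposure can remain in the study.
- *Study exit means withdrawal.* The term is undefined and would naturally also cover completing 36 months.
- *The historic cohort is followed to death.* Its follow-up is not described. It is free of withdrawal, but may be incomplete for other reasons.
- *Withdrawal is informative and the bias large.* No reasons for leaving are given. If patients leave close to death, little person-time is lost, and the 3% rows apply. If they leave because they feel well, the bias is small or reversed.

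It can also be said that an article leaves the handling of data after withdrawal to the full protocol or analysis plan, and that medical records are already a named source, so later admissions may in fact be available.

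All four cautions stand, and they limit what can be claimed about size. The point about scope stands only in part. The article does not merely omit the end of the window: it states one, and that stated rule excludes admissions after withdrawal. An analysis plan cannot restore events that were not collected, and naming a data source does not say that it is read past exit.

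**Conclusion.** The concern holds in a limited form. As written, admissions after withdrawal are outside the primary outcome in the intervention cohort, about 48 of 240 patients could be affected if all planned attrition is withdrawal, and the promised ITT analysis does not cover the full follow-up for them. A historic cohort cannot be truncated by this rule.

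The size depends on the summary used and on assumptions that the article cannot settle. A total to exit is too low even with uninformative withdrawal. For a rate, with no true effect, the spurious reduction is:

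- 0 if the rates are equal
- about 0.2 to 0.4 days/year if 3% of person-time is lost at 2 to 3 times the average rate
- about 0.4 to 0.8 days/year if 10% is lost at 1.5 to 2 times

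The 1.6 days/year from 10% lost at 3 times the average is an extreme case. Against a target of 2 days/year, the middle of this range is enough to matter. That the bias is present, or that it favours the intervention, is a risk and not an established fact.

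**What to change.** - End the primary outcome window at death or 36 months from the initial visit, in place of death or study exit.
- Separate two events: stopping the conversations or visits, and withdrawing consent to the use of records.
- For every enrolled patient who does not object, extract admissions and date of death from medical records to that end point, whether or not visits continue.
- Apply the same window to the historic cohort, and state its start and end.
- Define the ITT set as all enrolled patients over that window.

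The cost is protocol and consent wording, plus record look-up for up to about 48 patients; no extra visits are needed. Patients who refuse record use remain censored. The change is best made early, because what may be collected after withdrawal depends on the consent given.

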## Introduction

Worldwide, liver cirrhosis ranks as the 11th most common cause of death. In 2019, it accounted for an estimated 1.48 million deaths, reflecting an 8.1% increase since 2017 [1]. The distribution of cirrhosis etiologies and their prevalence varies across countries, largely due to differences in lifestyle factors such as alcohol consumption, obesity, and the risk of viral hepatitis. In Europe, alcohol-related liver disease (ARLD) is currently the leading cause of cirrhosis-related deaths [2].

Liver cirrhosis is the end stage of chronic liver disease of all causes, resulting from sustained inflammation that progresses to fibrosis and, ultimately, liver failure. The progression of liver cirrhosis is divided into a compensated stage, characterized by an absence of specific symptoms and apparent complications, and a decompensated stage featuring one or more severe complications such as ascites, hepatic encephalopathy, infection, renal dysfunction, and variceal bleeding [3]. At this stage, the patient often experiences fatigue, nausea, malnutrition and increasing frailty due to loss of muscle mass. This transition from compensated to decompensated liver cirrhosis significantly worsens health-related quality of life (HRQoL) scores [4, 5], while median survival decreases dramatically from approximately 12 years to just two years [6, 7]. Patients with decompensated liver cirrhosis experience some of the highest rates of unplanned hospital admissions, with 1.5 to 3 liver-related admissions per year [8–12].

The current management of decompensated liver cirrhosis focus on symptom relief, the prevention of further complications, and, if possible, liver transplantation, which remains the only curative option [7–14]. According to the World Health Organization, palliative care should be integrated alongside life-prolonging medical treatment as part of a cohesive approach to care, focusing on enhancing the quality of life for patients and their informal caregivers facing the challenges of serious illnesses. Palliative care aims to prevent and relieve suffering through early identification, assessment, and treatment of physical, psychosocial, and spiritual symptoms and concerns [15].

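### The primary outcome is a total over unequal follow-up, the named tests ignore time at risk, and the sample size is in days per year: one quantity is powered and another is defined

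*Protocol article*

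**What the plan says.** All places are in the protocol article.

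- **Primary outcome**: healthcare system burden is "measured as the number and length of hospital admissions from the initial visit to death or study exit". It is "compared to a recent historic cohort of a similar size from the involved centers". The start point and length of observation of that cohort are not given.
- **Intervention elements**: after the first conversation and one at 4–10 weeks, conversations take place "at 6, 12, 18, 24, 30, and 36 months, or until withdrawal from the study or death".
- **Introduction**: on decompensation, "median survival decreases dramatically from approximately 12 years to just two years".
- **Sample size**: "we assumed the historical cohort will have an average of seven days in hospital per year", and the authors "hypothesize that the intervention will cause a reduction of two days/year with an assumed SD of 7 days". This gives 199 participants, raised to 240 for an estimated 20% attrition.
- **Statistical methods**: numerical outcomes are compared with an unpaired t-test if normally distributed, or "the Wilcoxon-Mann-Whitney test for non-normally distributed numerical data". Differences are reported as means with standard errors and 95% confidence intervals. No rate, offset or fixed window is mentioned.
- **Health economic outcomes**: the cost-effectiveness analysis also counts admissions and their length for each patient across follow-up, not per unit of time.

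**The concern.** A patient who dies or leaves at three months has three months in which to accumulate hospital days; one who stays to the end has 36. A total over that window mixes how often a patient is in hospital with how long the patient is observed. In a randomised trial one might hope for similar follow-up in both groups. Here the comparator is a non-randomised historic cohort with an unstated window. Intervention patients can withdraw consent, and historic patients have no matching route out. All-cause mortality is not a listed outcome, so a difference in survival would not be visible beside the hospital days.

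Earlier death or exit in the intervention group would then look like less hospital use, and longer survival like more. The sample size does not reveal this, because it is on a per-year scale that neither the outcome definition nor the methods section carries over.

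The rule for choosing the test adds a smaller problem. With a mean of 7 and an SD of 7, a non-negative variable cannot be normal, so the rule points to the rank test. That test does not address the 2-day mean difference used for sizing.

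**Working it through.** **1. The plan's own figure.** Inputs from the Sample size section: difference 2 days/year, SD 7. Two-sided 5% and 80% power are assumed, as neither is stated.

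n per group = 2 × (1.96 + 0.8416)² × 7² / 2² = 2 × 7.849 × 12.25 = 192.3, so 193; the t-based solution is 194. The stated 199 is within 3% of this. As a group size, 199 gives 81% power; as a two-group total it gives 52%. So 199 is the intervention group, set against a historic cohort of similar size, and the calculation is entirely in days per year.

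**2. Follow-up under an assumed survival curve.** Assumptions: exponential survival with a 2-year median (a figure the Introduction gives as background), a 36-month cap, and 7 days/year in both groups, constant until death.

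- Monthly death hazard h = ln 2 / 24 = 0.02888.
- Mean follow-up = (1 − exp(−36h)) / h = 22.4 months.
- Mean total = 7 × 22.38 / 12 = 13.06 days.

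**3. Same true rate, shorter follow-up in the intervention group.**

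| Assumed difference | Mean follow-up (months) | Mean total (days) | Spurious difference (days) |
|---|---|---|---|
| None | 22.4 | 13.06 | 0 |
| Withdrawal hazard −ln(0.8)/3 = 0.0744 per year (20% over 3 years if nobody died) | 20.4 | 11.93 | −1.1 |
| Withdrawal hazard 0.0104 per month (20% actually withdraw before death or month 36) | 19.3 | 11.24 | −1.8 |
| Death hazard ratio 1.3 (h = 0.03755) | 19.7 | 11.52 | −1.5 |

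**4. Effect on the tests.** Simulations used 240 per group with no true difference in rate; the nominal rate of false benefit is 2.5%.

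- First withdrawal reading, days per year with mean 7 and SD 7: 12% (t-test) and 14% (Wilcoxon).
- Second reading, clustered admissions with mean stays of 3.5 or 7 days: 18–20% and 21–26%.
- Death hazard ratio 1.3, clustered admissions: 11–15% and 15–16%.
- Total days divided by total person-years, with a robust variance: 2–3% in the withdrawal and hazard-ratio scenarios run with it.

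These percentages depend on the assumed spread of hospital days. A further run of the two withdrawal readings crossed each with three spreads (annual SD 7, or exponential frailty with stays averaging 3.5 or 7 days) and gave about 8% to 32%. They show the order of magnitude only.

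**5. If admissions cluster near death.** Replace the constant rate by 5 days/year plus an assumed 10 days per death. The proportion dying within 36 months is 64.6% at hazard ratio 1.0 and 74.1% at 1.3; mean follow-up is 1.865 and 1.645 years.

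- Totals: 5 × 1.865 + 10 × 0.646 = 15.8, and 5 × 1.645 + 10 × 0.741 = 15.6 days.
- Rates: 15.79 / 1.865 = 8.5, and 15.64 / 1.645 = 9.5 days per person-year.

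Here the total hardly moves and the rate rises by one day per year.

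**6. Normality.** P(N(7, 7) < 0) = Φ(−1) = 15.9%, for a quantity that cannot be negative.

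**The case against.** The strongest reply is that annualising is the natural reading. The hypothesis is stated in days per year, the list of tests is generic, and offsets and the handling of death are usually left to an analysis plan. A reader might infer from the article that the trial will analyse raw totals; it does not show that. What stands is the conflict: the outcome, its window and the tests are fixed in print on one scale and the sample size on another, and the health economic section repeats the total.

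Four further readings are tempting, and the documents do not support them.

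- *That 20% are expected to withdraw.* The article says attrition, which may include deaths.
- *That the bias favours the intervention.* The historic window is not given, so the direction is unknown.
- *That an ineffective programme would be declared effective.* At the rates shown above, most such trials would not be.
- *That a person-year rate cures everything.* Step 5 shows that differential death can distort the rate when hospital use rises before death, while the artefact in totals shrinks.

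On the test rule, mean differences with confidence intervals are reported in any case, so the 2-day contrast would still be estimated. The choice of test is the lesser part of this point.

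**Conclusion.** The point holds as an inconsistency within the article that can affect the primary conclusion. Following the text literally compares totals over unequal follow-up, although the trial is sized on a rate.

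Under the constant-rate assumptions, plausible imbalances in follow-up create a spurious difference of about 1.1 to 1.8 days per patient. For one-sided withdrawal, false benefit runs at roughly 12% to 26% instead of 2.5%. These figures rest on survival, withdrawal and dispersion assumptions that the article does not supply. The sign reverses if the historic cohort has the shorter follow-up, and the mortality component shrinks if admissions cluster near death. The inconsistency itself depends on none of these assumptions.

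**What to change.** 1. **Outcome.** Carry the days-per-year scale of the sample size into the Primary outcome and Statistical methods sections: hospital days, and admissions, per person-year under observation.
2. **Analysis.** Use a count or rate model with log follow-up time as offset and robust or overdispersed standard errors. Report the rate ratio and the difference in days per year. Drop the normality-driven choice of test for this outcome.
3. **Historic cohort.** Apply the same eligibility, start point and maximum window as in the intervention group.
4. **Death.** Report all-cause mortality for both cohorts beside the primary result, and add a fixed-window sensitivity analysis, such as days alive and out of hospital over 12 months.

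The cost is some redrafting and a modest amount of extra analysis. Entry, exit and death dates must be available for both groups. The article does not list them among the data collected, so their availability in the historic cohort should be confirmed first.
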